### **2.6 SAMPLE SIZE**

The target sample size is based on the hypothesis that the combined use of UHF and steroids versus the LMWH group will significantly reduce the risk of 28-day death. The overall sample size in this study is expected to be 210 with a randomization 1:1:1. Assuming an alpha of 2.5% (two tailed) and mortality rate in LMWH group of 50%, as indicated from initial studies of ICU patients, the study will have an 80% power to detect at least a 25 % absolute reduction in the risk of death between:

a) LMHW + steroids group and LMWH group

or

b) UHF + steroids group and LMWH group

The study has not been sized to assess the difference between LMHW + steroids group and UHF + steroids group, therefore the results obtained from this comparison will need to be interpreted with caution and will need further adequately sized studies to be confirmed.

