## **4.2 STATISTICAL METHODS**

### **4.2.1 Methods for statistical analysis**

All patients enrolled in the study will be entered in the full analysis set independently of his/her treatment time. The intention to treat population will be considered for primary analysis. A descriptive statistical analysis will be performed to describe every relevant variable. In general, categorical data will be presented using counts and percentages, whilst continuous variables will be presented using the number of patients, mean, standard deviation, median, minimum, and maximum. Denominators for calculation of percentages will be taken as the number of non-missing responses in the specified analysis population and treatment group unless otherwise stated, and percentages will be rounded to one decimal. Minima and maxima will usually be reported to the same level of accuracy as the raw data; means, medians and standard deviations will be presented to one further decimal place; standard errors (if presented) will be presented to 2 decimal places more than the raw data. 97.5 % confidence interval will be calculated for primary outcome and for the relevant secondary ones. All data recorded in the CRF will be listed. Distribution of SAPSII and SOFA score (total and for single organ) at admission, P/F ratio distribution at baseline and at day 3, biomarkers PCR, PCT and IL-6 P/F ratio distribution at baseline and at day 3 will be summarized.

The comparison between

1. LMHW + steroids group and LMWH group
2. UHF + steroids group and LMWH group

with binary outcomes will be performed by using Relative Risks (RRs), whereas for continuous data, the difference of means (DMs) will be used. Comparisons involving time to event data will be displayed by using Kaplan-Maier survival curves and summarised by Hazard Ratios (HRs).

All measures of association will be presented with their confidence intervals. A result will be considered as statistically significant if its p-values will be less than 0.025 (2.5%).

The analyses will be performed by using STATA software.

As the study has not been sized to assess the difference between LMHW + steroids group and UHF + steroids group, the results obtained from this comparison will be reported and will be interpreted with caution. The main analyses will not take into account the factors of stratification.

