#### Analyses ad interim

Considering a statistical approach based on two phases, an interim analysis is planned after the randomization of 90 patients (50% of sample size) for the double objective of monitoring safety and verifying the accuracy of the assumptions made for sample size estimation regarding the primary end-point event rate in relation to the anticipated survival benefit. With the interim analysis we will be able to evaluate whether there is a substantial superiority of one treatment. The obtained results will be evaluated by the DSMB and by the steering committee and, in case of significant differences in survival among the groups, all patients will be switched to the most promising treatment.

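### The interim trigger (a survival difference among three groups) does not support the conclusion drawn from it (one best treatment), because it never tests the two steroid groups against each other

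*Protocol*

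**What the plan says.** Protocol section 5.1, under the interim heading, states the question as one about a single winner: "With the interim analysis we will be able to evaluate whether there is a substantial superiority of one treatment". The next sentence gives the trigger and the action. After evaluation by the DSMB and the steering committee, "in case of significant differences in survival among the groups, all patients will be switched to the most promising treatment". The paragraph gives no test, no boundary and no definition of most promising.

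The timing is early: "an interim analysis is planned after the randomization of 90 patients (50% of sample size"). With 1:1:1 allocation that is about 30 patients per arm.

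Section 2.6 sizes two contrasts, each steroid group against LMWH, and excludes the third: "The study has not been sized to assess the difference between LMHW + steroids group and UHF + steroids group". Section 4.2.1 repeats the exclusion and says that "the results obtained from this comparison will be reported and will be interpreted with caution". Section 4.2.1 also gives the protocol's only significance threshold, p below 0.025.

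**The concern.** The trigger and the conclusion answer different questions. Rejecting equality of three groups shows that some groups differ. Finding that a steroid group beats LMWH shows just that. Neither shows that the leading group beats the runner-up, which is what naming one superior treatment requires.

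The gap matters under the protocol's own planning assumptions. Section 2.6 plans the same 25-point reduction for either steroid group against LMWH. If steroids carry the benefit, the trigger is met because LMWH alone does worse. The single treatment then has to be chosen between two groups that the trigger has not compared. The protocol asks for caution on that comparison at 70 per arm, yet the interim clause lets it determine the treatment of all patients at about 30 per arm.

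At stake is a claim that one heparin strategy given with steroids is better than the other, on data that cannot separate them. Moving everyone to one group would also cut short the randomised Group 2 versus Group 3 comparison that section 4.2.1 promises to report.

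**Working it through.** **Inputs.** From section 2.6: 210 patients, 1:1:1, two-sided alpha 0.025, LMWH mortality 50%, reduction of 25 points, power 80%. From section 5.1: look at 90 patients, so 90/3 = 30 per arm. From section 4.2.1: threshold p<0.025. Applying that threshold to the interim is an assumption, because none is stated there.

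**The plan's own figure.** Two proportions, pooled variance, no continuity correction, mean proportion (0.50 + 0.25)/2 = 0.375:

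n = [2.2414 × √(2 × 0.375 × 0.625) + 0.8416 × √(0.5 × 0.5 + 0.25 × 0.75)]² / 0.25²
= [1.5346 + 0.5567]² / 0.0625 = 69.97, so 70 per arm and 210 in total. The stated size is reproduced.

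**Interim calculation.** Let a, b and c be deaths in Groups 1, 2 and 3, each binomial with 30 patients. Sum Bin(a; 30, p1) × Bin(b; 30, p2) × Bin(c; 30, p3) over all outcomes that meet the trigger, and record which group has fewest deaths. Because no test is named, two readings were computed:

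- **Global:** three-group chi-square on 2 df, p<0.025.
- **Pairwise:** either steroid group versus LMWH, pooled z-test, p<0.025.

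Each cell gives global / pairwise. All columns after the second are conditional on the trigger being met.

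| True mortality, Groups 1/2/3 | Trigger met | Group 2 strictly lowest | Group 3 strictly lowest | Tie | Groups 2 and 3 differ at p<0.025 |
|---|---|---|---|---|---|
| 50/25/25% | 44.1 / 57.3% | 44.6 / 45.8% | 44.6 / 45.8% | 10.9 / 8.5% | 5.1 / 4.1% |
| 50/25/30% | 36.0 / 49.5% | 64.8 / 66.2% | 26.2 / 27.1% | 9.0 / 6.7% | 9.4 / 7.0% |
| 50/25/35% | 31.7 / 45.0% | 81.8 / 82.5% | 12.5 / 13.3% | 5.7 / 4.2% | 21.5 / 15.1% |

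By symmetry, the last two rows hold with Groups 2 and 3 exchanged.

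**Sensitivity, with Groups 2 and 3 equal.**
- At 50/35/35%, the trigger is met in 14% / 24%.
- At 50/25/25% with threshold 0.05, it is met in 56% / 68%.
- With 35 per arm (half of 210), it is met in 52% / 65%.
- With 20 per arm evaluable (assuming some patients lack day-28 data), it is met in 28% / 41%.
- In each case the choice still splits evenly between Groups 2 and 3.

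**Power of the missing comparison.** For 25% versus 35% at 30 per arm and alpha 0.025:

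Φ{[0.10 × √30 − 2.2414 × √(2 × 0.30 × 0.70)] / √(0.1875 + 0.2275)} = Φ(−1.40) = 8%.

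At 70 per arm the same formula gives 17%.

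**The case against.** **The trigger may be loose wording.** The sentence before it asks about superiority of one treatment, and section 4.2.1 specifies only the two contrasts against LMWH. It is fair that the protocol names no test, so the three-group test is one reading and not a stated fact. But the LMWH contrasts do not rank the steroid groups either, so both readings leave the same gap.

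**People decide, not a formula.** The DSMB and steering committee evaluate the results first, and a DSMB charter that is not shown may hold criteria. A reader might infer that the switch is automatic or irreversible; the text says neither. It does commit to a switch once differences are significant, and gives no criterion for choosing between two good groups.

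**A chance choice with a bleeding cost.** A reader might infer that two groups with similar deaths would be separated by chance, with a bleeding consequence because heparin intensity differs. The documents do not establish this. Safety is a stated aim of the same interim, bleeding is a safety endpoint, and nothing says it would be ignored.

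**Inflated error.** A reader might set 44-57% against 2.5% and call it an 18- to 23-fold inflation. That is not valid. Those rates are mostly power to detect a real benefit over LMWH, whereas 2.5% is a type I error rate for a different contrast.

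**Errors shrink as the true gap grows.** This stands. With equal steroid groups, either choice costs nothing on mortality. With a 10-point gap the worse group looks best in about 13%, and with a 15-point gap (50/25/40%) in about 5%. If only one steroid group works (50/50/25%), it is picked in 98-99%. The near-even split applies only when the groups are equal and the trigger is met.

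**Conclusion.** The point holds as a mismatch between trigger and conclusion. On either plausible reading, the condition for action does not test whether the leading group beats the runner-up. The clause also conflicts with sections 2.6 and 4.2.1, which treat that comparison as unsized.

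At the planning rates with equal steroid groups, the condition is met in 44-57% of trials, and only 4-5% of those show a significant Group 2 versus Group 3 difference. If one steroid group is truly 5 points worse, it still looks best in 26-27% of triggered trials, plus 7-9% ties.

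These figures assume p<0.025 at the interim, 30 evaluable patients per arm, and selection by lowest observed day-28 mortality. Equal 25% mortality in both steroid groups fits section 2.6 but is not fixed by it. Changing the threshold or timing alters how often the trigger is met, but does not supply the missing comparison.

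**What to change.** Reconcile the interim paragraph of section 5.1 with sections 2.6 and 4.2.1:

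1. Name the two sized contrasts, each steroid group versus LMWH, as the interim efficacy comparisons, in place of a difference among the groups.
2. State that crossing on either contrast supports a conclusion about that group versus LMWH only, and does not rank Group 2 against Group 3.
3. Require the direct Group 2 versus Group 3 contrast to meet its own pre-stated interim threshold before one steroid group is declared superior to the other.

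What patients receive after a crossing is for the sponsor and DSMB to define; this point takes no position on it.

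As an illustration, suppose item 3 used p<0.025. With truly equal steroid groups (50/25/25%, 30 per arm), the chance of meeting the trigger and also declaring one steroid group superior would be 0.441 × 0.051 = 2.2% (global) or 0.573 × 0.041 = 2.3% (pairwise).

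The cost is a wording amendment to section 5.1, carried into the DSMB charter, with no extra patients or data. The downside is that an interim crossing may no longer name a single winning arm. With about 8% power for a 10-point gap, the direct contrast will seldom settle the ranking at this look.

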### **5.2 Harms**

All the patients, regardless the inclusion in the study and the randomization group, will benefit from the best standard of care following the principles of Good Clinical Practice. Intensive care patients frequently develop life-threatening organ failure unrelated to study interventions and despite optimal management. Therefore, events that are part of the natural history of the primary disease process or expected complications of critical illness  will not be reported as adverse events (AE) in this study. All the included patients will be intensively monitored following the standard procedures of the Intensive Care and any suspected protocol-related AEs will be reported. The steering committee (SC) and the DSMB will evaluate the adverse events occurred during the study. For every AE, the SC and the DSMB must assess the intensity (severity) and causality (relationship to study treatment). Specifically, the intensity of events should be classified as mild, moderate, or severe. The assessment of causality will be based upon the categories of related and not related. These classifications should be based on the following definitions:

The intensity (severity) of a specific event is defined as follow:

Mild: AE which is easily tolerated;

Moderate: AE sufficiently discomforting to interfere with daily activity;

Severe: AE which prevents normal daily activities.

Causality assessment is required for all clinical investigation cases. The relationship between an AE and a product is considered:

Possibly related: if, after careful assessment, a possible connection with the use of the investigational product cannot be ruled out;

Not-related: if the AE is due to causes not related to the investigational product.

Events considered “Possible” related to the study treatment, if considered unexpected, will be reported to appropriate regulatory authorities.

All AEs which occur during the course of the study should be recorded within 24 hours in the eCRF. Information on the AE must be recorded on a specific AE form (included in the Investigator’s Site File) and forwarded to the DSMB and to the safety board. Moreover, the eCRF will ensure that an automatic email will be generated and sent directly to the Principal Investigator accountable to receive the study safety information. Each Investigator will be informed of all AE which are reported from other Investigators periodically.

During the course of the clinical trial, the investigators shall report any serious unexpected suspected adverse event to the EC which approved the protocol and to the Competent Authorities as soon as possible and in no event later than:

- (a) seven calendar days after becoming aware of the information if the event is fatal or life threatening; and
- (b) fifteen calendar days after becoming aware of the information if the event is neither fatal nor life threatening.

The investigators will, within eight days after having informed the EC, submit a complete report in respect of that information that includes an assessment of the importance and implication of any findings made.

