#### **1.1.2 Benefits on the use of steroids**

Studies on community-acquired pneumonia show that the excessive production of locally pulmonary cytokines induced by pulmonary infection may cause a severe host inflammatory response inducing pulmonary dysfunction, increasing ICU admission and mortality. Steroids exert potent anti-inflammatory activity by inhibition of leucocytes extravasation, function of macrophages and antigen-presenting cells, production of TNF-alpha, interleukin-1 and nitric oxide. A Chinese report on 201 patients with COVID-19 pneumonia pointed out a survival benefit of more than 15% among patients with ARDS who received Methylprednisolone compared to those who did not.

An interesting report on post-mortem pathological findings in a SARS-CoV-19 patient with ARDS found out interstitial mononuclear inflammatory infiltrates dominated by lymphocytes, in both lungs, implying a severe

immune injury, pulmonary oedema and hyaline membrane formation, finding that suggest a possible role of steroids in this disease' treatment.

Nonetheless, corticosteroid treatment is a double-edged sword and their use remains controversial.

World Health Organization (WHO) recommend against the systematic use of corticosteroids for treatment of viral pneumonia. This recommendation is mainly driven by retrospective observational studies led on SARS, MERS and influenza virus showing no survival benefit and a decelerated viral clearance without affecting the outcome together with the consideration of the many steroid-related possible harms such as secondary infections, gastro-intestinal bleeding and long-terms side-effects.

On the other hand, WHO itself through the Blueprint process has prioritized studies on steroids as an additional therapy that can improve patients' outcome in order to identify actions that can save lives in the immediate aftermath of the COVID-19 pandemic.

Because of methodological limitations in the available evidence, some scientific societies such as Chinese Thoracic Society have developed an expert consensus statement sustaining the use of corticosteroids in 2019-nCoV pneumonia.

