### **2.2 ELIGIBILITY CRITERIA**

#### **2.2.1 Inclusion Criteria**

1. Positive SARS-CoV-2 diagnostic (on pharyngeal swab of deep airways material)
2. Positive pressure ventilation (either non-invasive or invasive) from > 24 hours
3. Invasive mechanical ventilation from < 96 hours
4. P/F ratio  $\leq 150$
5. D-dimer level  $\geq 6$  x upper limit of local reference range
6. PCR  $\geq 6$  fold\_upper limit of local reference range

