- Routine laboratory test parameters for organ function assessment: haemoglobin, platelets count, white blood cells count, troponin, coagulative parameters (INR, PT, aPTT), parameters for liver (AST, ALT, bilirubin) and renal function (creatinine) will be recorded daily from inclusion to day 7 and then at day 14, 21, 28, censored at ICU discharge;
- Blood cells count, C-reactive protein (CRP) and procalcitonin (PCT), IL-6, immunoglobulins titers (IgG, IgA, IgM) will be recorded daily from inclusion to day 7 and then at day 14, 21 and 28, censored at ICU discharge;
- Beta-D Glucan in the blood and/or Galactomannan in the BAL will be recorded at admission and then every 3-5 days, censored at ICU discharge
- Ventilation mode (spontaneous breathing or mechanical ventilation), inspired oxygen fraction and arterial blood gas analysis parameters will be recorded daily from inclusion to ICU discharge, censored at day 28;
  - Adjunctive treatment such as pronation cycles, Nitric Oxide or ECMO will be recorded daily from inclusion to ICU discharge from (censored at day 28);
- New blood, respiratory and urinary-tract infections and the implicated microorganisms will be recorded from randomization to day 28;
- Viral reactivation measured by ADENOVIRUS, HSV e CMV DNA titres will be recorded from randomization to day 28, censored at ICU discharge;
- Need of renal replacement therapy: from randomization to 28 days, censored at ICU discharge.

D) Primary Outcome:

- All-cause mortality will be measured at day 28.

E) Secondary Outcomes:

- All-cause mortality will be measured at ICU discharge and hospital discharge
- SOFA score and its components will be recorded daily from randomization to ICU discharge (censored at day 28);
- Ventilation free days (VFDs) at day 28, measured at day 28;
- ICU free days (IFDs) at day 28, measured at day 28;
- Need of rescue administration of high-dose steroids or immune-modulatory drugs, measured from randomization to ICU discharge, censored at day 28;
- Switch from non-invasive to invasive mechanical ventilation from randomization to ICU discharge, censored at day 28;
- Occurrence of new infections will be recorded from randomization to day 28;
- Occurrence of objectively confirmed venous thromboembolism, stroke or myocardial infarction will be recorded from randomization to day 28;
- Occurrence of protocol related adverse events (see chapter 5.2) at day 28 (safety endpoint).

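### The severity scale in section 5.2 does not fit ventilated ICU patients, and the adverse-event safety endpoint in Appendix 4 is open to attribution bias in either direction

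*Protocol*

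**What the plan says.** **Severity.** Section 5.2 requires each adverse event to be classed as mild, moderate or severe. Mild means easily tolerated. The other two grades are "Moderate: AE sufficiently discomforting to interfere with daily activity" and "Severe: AE which prevents normal daily activities". The scale stops there. The expedited-reporting rules at the end of the same section use a different distinction: whether an event is fatal or life-threatening.

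**Population.** Section 2.2.1 requires "Positive pressure ventilation (either non-invasive or invasive) from > 24 hours" and a P/F ratio of 150 or less.

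**What is counted.** Section 5.2 says that natural-history events and "expected complications of critical illness" are not reported as adverse events, and that "any suspected protocol-related AEs will be reported". Later it says: "All AEs which occur during the course of the study should be recorded within 24 hours in the eCRF". The steering committee and the DSMB assess severity and causality. An event is possibly related if a connection with the investigational product cannot be excluded. Section 3.1 makes the trial open-label for patients and all care staff.

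**Endpoint.** List E of Appendix 4 includes "Occurrence of protocol related adverse events (see chapter 5.2) at day 28 (safety endpoint". Section 2.4.2 does not list this endpoint. It labels two other outcomes as safety endpoints, major bleeding and clinically relevant non-major bleeding, and neither is in list E.

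**The concern.** There are two separate problems.

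First, a scale based on daily activity presupposes a patient who has daily activities to lose. A patient ventilated in intensive care has none, and a sedated patient cannot say how well an event is tolerated. The compulsory grade then tells the reader little about how serious an event was.

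Second, an endpoint restricted to protocol-related events measures both the harm and the readiness of assessors to link it to a drug. The arms contain different drugs, and the people who first raise the suspicion know the arm. Section 1.1.2 itself names "steroid-related possible harms such as secondary infections, gastro-intestinal bleeding and long-terms side-effects". Infection and gastrointestinal bleeding can also be seen as complications of critical illness, so the same event may be counted as related or dropped as expected, and the protocol does not say which. At stake is whether a difference in this endpoint, or its absence, can be read as a difference in harm.

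**Working it through.** **1. Severity scale against population.** At entry, normal daily activities are already prevented by the illness and the ventilation. Moderate requires interference with daily activity and severe requires its prevention. When there is no activity left, neither criterion gives an assessor anything to observe, so the line between the two grades is arbitrary. Mild can still be used for a trivial event in a patient able to tolerate it visibly. No grade corresponds to life-threatening or fatal, so the grade cannot feed the reporting rule of seven or fifteen days.

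**2. Path of an event into the Appendix 4 endpoint.**
- Site staff, who know the arm, decide whether the event is an expected complication (dropped) or suspected to be protocol-related (reported).
- The steering committee and the DSMB then judge causality. Blinding of either is not stated.
- The test is whether a link to the investigational product can be excluded. Groups 2 and 3 are assigned methylprednisolone and group 1 is not. For an infection, the test can therefore give different answers in different arms even if infection is equally frequent.

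**3. What such a filter can do.** The protocol gives no rate or power for adverse events, so the rates and attribution shares below are assumptions. Only the arm size and the significance level come from the protocol.

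Arm size: section 2.6 gives 210 patients at 1:1:1, or 70 per arm. This reproduces from n = [z(1−α/2)·√(2p̄(1−p̄)) + z(power)·√(p₁(1−p₁)+p₂(1−p₂))]² / (p₁−p₂)², with p₁ = 0.50, p₂ = 0.25, two-sided α = 0.025 and power 0.80: (2.241 × 0.685 + 0.842 × 0.661)² / 0.0625 = 70 per arm. The sample size is not in question here.

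Observed rate = true rate × share attributed. The last column is the probability of a significant result in the direction shown, from the same normal approximation (70 per arm, two-sided α = 0.025).

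| True rates | Shares attributed | Observed rates | Probability |
|---|---|---|---|
| 20% v 40% | all counted | 20% v 40% | 64% |
| 20% v 40% | 50% v 50% | 10% v 20% | 28% |
| 20% v 40% | 20% v 20% | 4% v 8% | 11% |
| 20% v 40% | 50% v 25% | 10% v 10% | difference gone |
| 40% v 40% | 20% v 30% | 8% v 12% | 7% (false) |
| 40% v 40% | 25% v 50% | 10% v 20% | 28% (false) |
| 40% v 40% | 20% v 60% | 8% v 24% | 64% (false) |

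Even attribution weakens a true difference. Uneven attribution can erase one or create one. The table shows both directions; it does not predict which would occur.

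**4. What is collected without attribution.** Section 2.4.2 counts major bleeding, clinically relevant non-major bleeding, new infections to day 28, and confirmed venous thromboembolism, stroke or myocardial infarction. None requires a judgement of relatedness. Platelet counts are recorded under section 2.4.3 and Appendix 4. Heparin-induced thrombocytopenia appears as an exclusion criterion (section 2.2.2) but has no outcome of its own.

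**5. Consistency.** The adverse-event endpoint is in Appendix 4 but not in section 2.4.2. The two bleeding endpoints are in section 2.4.2 but not in list E. Section 5.2 names the causality categories as related and not related, then defines possibly related and not related.

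**The case against.** The strongest reply is that the protocol does not depend on this endpoint to compare harm. The bleeding outcomes are largely criteria-based, infections and thromboembolic events are counted whatever their cause, and the DSMB has access to all results under section 5.1. That stands, and it limits the consequence considerably. It does not repair the Appendix 4 endpoint.

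Four stronger readings are tempting, and the documents do not support them:

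- *The endpoint cannot separate the arms.* It is an occurrence endpoint and does not use the severity grade, so a poor scale does not block the comparison. Biased attribution may even produce a separation.
- *Every in-ICU event would be graded severe.* The definition concerns an event that itself prevents activity, so prior incapacity does not automatically make each event severe. Mild remains usable, entry allows non-invasive ventilation, and day 28 may fall after ICU discharge.
- *Unblinded site staff alone decide what counts.* They apply the first filter. The formal causality call belongs to the steering committee and the DSMB, which is described as independent. The low threshold for a possible link also works against wholesale dismissal, though it makes the answer depend on which drugs the arm contains.
- *The two recording instructions flatly contradict each other.* The second may mean all adverse events left after the exclusion. That is a reasonable reading, but the text does not state it.

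Excluding expected complications of critical illness is a stated and referenced choice and is not itself the fault.

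**Conclusion.** The concern holds as two limited defects. The severity scale is unsuited to patients who enter ventilated with P/F at or below 150, and it lacks the levels that the reporting rules need; this follows from the text alone. The Appendix 4 adverse-event endpoint is exposed to attribution bias of unknown direction. The size cannot be derived from the documents: the range of 7% to 64% for a false difference, and the fall in power from 64% to between 28% and 11%, rest wholly on assumed event rates and attribution shares. The mismatch between section 2.4.2 and Appendix 4 leaves unclear which outcomes form the safety comparison. It would be wrong to conclude that safety cannot be compared in this trial; the attribution-free outcomes in section 2.4.2 can carry that comparison.

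**What to change.** 1. Replace the daily-activity scale with grades based on clinical consequence that can be read from the chart: no intervention needed; intervention or change of study drug needed; life-threatening or needing organ support; fatal.
2. Base the between-arm safety comparison on the bleeding and infection outcomes already defined in section 2.4.2, and add heparin-induced thrombocytopenia, all counted in every arm regardless of suspected relationship. Keep relatedness for expedited reporting only. The exclusion of expected ICU complications can stay for other events.
3. List the same safety endpoints in section 2.4.2 and Appendix 4. State whether the instruction to record all adverse events applies after the exclusion of expected complications. Use one set of causality categories.

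The cost is protocol wording, revised categories on the adverse-event form and slightly more events to enter. Bleeding, infections and platelet counts are already collected. One limit remains: part of the non-major bleeding definition turns on the decision to interrupt a study drug, which is taken by staff who know the arm. Ignoring attribution therefore reduces open-label bias but does not remove it.
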